## Methods

### Study population

Sixty adult patients with either non-metastatic or metastatic solid tumours will be included in the study. Briefly, 30 women with breast cancer whose, (i) 10 HER2-positive (5 non-metastatic and 5 with a first metastatic evolution), (ii) 10 HER2-negative (5 non-metastatic and 5 with a first metastatic evolution), (iii) 10 on hormone replacement therapy (5 non-metastatic and 5 with a first metastatic evolution), 10 women with an ovarian cancer grade III and IV, 10 men and 10 women with a metastatic non-small cell lung cancer and 20 healthy donors will be included in the study (Fig. 1). Eligibility criteria for cancer patients are listed in Table 1. Additionally, 20 healthy volunteers with no previous cancer history, negative serology for HIV, HCV and HBC and aged 50 to 70 years old will also be included. Age group of healthy donors is in agreement with the average age of occurrence of the different solid tumours studied.

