**Fig. 1 Fig1:**
[figure not shown]
Study population

**Table 1 Tab1:** EXODIAG study inclusion and exclusion criteria for cancer patients

Inclusion criteria for cancer patients	
Women newly diagnosed with infiltrating non-metastatic breast cancer (positive or negative HER status or hormone therapy). Women with breast cancer with a first metastatic evolution (positive or negative HER status or hormone therapy).	
Women newly diagnosed with stage III and ICV ovarian cancer. Men and women newly diagnosed with metastatic non-small cell lung cancer.	
Patients older than 18 years. Performance status of 0 or 1 at the time of inclusion, according to the Eastern Cooperative Oncology Group (ECOG) and WHO.	
Affiliated to the French social security social or beneficiary of such a regimen.	
Written informed consent.	
Exclusion criteria for cancer patients	
Patient with another synchronous tumour.	
Men with breast cancer.	
Positive serology for HIV, HCV or HBV.	
Patients unable to undergo medical follow-up for geographical, social or psychological reasons.	
Pregnant or nursing women.	

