### Data collection

Data collected during the study will be recorded on a CRF for patients and healthy donors. On initial visit, age, sex, weight, height, medical history and special medication will be noted. In addition, healthy donors will be followed for a year and any change in treatments or intercurrent illness. Concerning patients, upon diagnosis and during medical follow-up, date of disease diagnosis, line of treatment, date and relapse type, metastasis/metastatic sites, surgical procedures, treatment modification, date of medical exams performed during assessments (radiographic, biological) and date of death will be noted.

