### Sample size and statistical analysis

A selected group of 60 patients, including 30 women with a breast cancer whose (i) 10 HER2-positive (5 non-metastatic and 5 with a first metastatic evolution), (ii) 10 HER2-negative (5 non-metastatic and 5 with a first metastatic evolution), (iii) 10 on hormone replacement therapy (5 non-metastatic and 5 with a first metastatic evolution), 10 women with an ovarian cancer grade III and IV, 10 men and 10 women with a metastatic non-small cell lung cancer and 20 healthy donors will be included in the study (Fig. 1). In this project, the main objective is to evaluate the feasibility of HSP70-exosomes dosing in patients with cancer: The assumptions related to baseline assays are as follows: a technically feasible dosage rate of 75% is considered to be insufficient, a 90% feasibility rate is expected, unilateral alpha = 5%, power = 90%, 10% rate of withdrawal of patient consent or study discontinuation before initial dosing. Based on these assumptions, using a one-step Fleming design, 60 subjects are required (55 + 10% = 60). At the end of the study on the first 55 patients included, if 47 or more patients had a dosage, the technique will be considered as having good feasibility.

In addition, baseline assays of the 60 patients will be compared with 20 controls, to confirm that exosome HSP70 is as a cancer specific marker. The mean of HSP70 in the controls is expected to be 0. It is expected to be around 2 for cancer patients with a common standard deviation of 2. With these hypotheses, bilateral alpha of 5% and 60 patients, we will have a power of more than 95% to compare exosome HSP70 concentrations between cases and controls.

Subgroup analyses, depending on the pathology, histological type and response to treatment, will be exclusively exploratory. These analyses will be carried to study whether variations in HSP70-exosome dosage at baseline and follow-up could be associated with these different variables.

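### The case-control comparison is stated with no age or sex control, although control age eligibility differs from the patients' and the text fixes no control sex mix.

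*Protocol article*

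**What the plan says.** Under Sample size and statistical analysis, the protocol article plans that "baseline assays of the 60 patients will be compared with 20 controls", "to confirm that exosome HSP70 is as a cancer specific marker". The planning assumptions are those of a two-mean comparison: "The mean of HSP70 in the controls is expected to be 0", and "It is expected to be around 2 for cancer patients with a common standard deviation of 2". Power is given as above 95% at a two-sided 5% level. No age or sex term, matching or stratification is named there for this contrast.

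The same concentration, in patients and cancer-free controls, is the primary endpoint (Study objectives and endpoints). The Discussion also intends to derive a threshold for detecting cancer.

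- **Age.** Table 1 admits "Patients older than 18 years" and sets no upper limit. Study population restricts healthy volunteers to 50 to 70 years, with this reason: "Age group of healthy donors is in agreement with the average age of occurrence of the different solid tumours studied".
- **Sex.** The quotas in Study population make the patients 50 women and 10 men. The text gives no corresponding figure for the 20 controls. Fig. 1, which describes the study population, is not available here.
- **Data.** Both groups have a case report form, and Data collection states: "On initial visit, age, sex, weight, height, medical history and special medication will be noted".

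**The concern.** A comparison that is meant to show cancer specificity should not be open to a simpler explanation. If HSP70-exosome concentration varies with age or sex, and the two groups differ in age or sex, part of the observed difference belongs to those factors. The error could go either way: a false signal, or a real one masked. It would carry over into any detection threshold derived from the same data.

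The age safeguard is partial. One 20-year range, chosen around an average for three tumour types, does not match the spread of patient ages. A patient younger than 50 or older than 70 has no control of comparable age, and modelling cannot supply one without extrapolation. For sex, the text states no safeguard.

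**Working it through.** **Inputs from the article.** 60 patients, 20 controls, difference 2, SD 2, two-sided 5%. Women: 30 breast + 10 ovarian + 10 lung = 50. Men: 10 lung. Male share 10/60 = 16.7%.

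**Inputs assumed, because the article gives none.** Number of male controls (0, 3, 10 or 15 of 20); sex effect of 0.5 or 1 SD; age effect of 0.2 SD per decade; gap in mean age of 5 or 10 years.

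**1. The stated power.** SE = 2 × √(1/60 + 1/20) = 0.516. Noncentrality = 2/0.516 = 3.87 on 78 degrees of freedom. Power is 96.9% (noncentral t) or 97.2% (normal approximation). With 54 or 55 patients assayed after the planned 10% loss, it is 96.5% or 96.6%. The claim of more than 95% reproduces.

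**2. False positives from sex, with no cancer effect.** Bias = (male share in patients − male share in controls) × sex effect. With 10 male controls and a 1 SD effect: (0.167 − 0.5) × 2 units = −0.67 units, so the noncentrality is 0.67/0.516 = 1.29 in absolute value. The table gives rejection rates for a 0.5 SD / 1 SD sex effect. The formula holds the SD at 2. The simulated t-test lets the sex effect also widen the spread within groups, so its rates are generally a little lower.

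| Male controls | Formula | Simulation |
|---|---|---|
| 0 of 20 | 6.2% / 9.8% | about 6% / 8% |
| 3 of 20 | 5.0% / 5.0% | 4.6% / 3.7% |
| 10 of 20 | 9.8% / 24.7% | 9.0% / 20.0% |
| 15 of 20 | 20.0% / 60.7% | 19% / 55% |

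**3. False positives from age.** Bias = gap × 0.2 SD per decade. Five years gives 0.1 SD = 0.2 units and 6.7% rejection. Ten years gives 0.2 SD = 0.4 units and 11.9%.

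**4. Could this explain the whole expected result?** Significance needs an observed difference of about 1.991 × 0.516 = 1.03 units. To produce the full difference of 2 through sex with half-male controls, the sex effect would have to be 2/0.333 = 6 units, or 3 SD.

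**5. Price of adjustment.** The variance is multiplied by 1/(1 − R²), where R² is the share of group membership explained by the covariates. Adjusting for age and sex, power is 96.1% at R² = 0.05, 95.2% at 0.10, 92.8% at 0.20 and 89.2% at 0.30. Adjusting for sex alone, it is 96.2%, 96.9%, 95.0% and 89.4% for 0, 3, 10 and 15 male controls.

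**The case against.** The strongest reply has four parts.

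- **Unadjusted analysis is not actually stated.** The article gives power assumptions and names no test. The full protocol and analysis plan are not shown and may contain covariates. This stands as far as model terms go: their absence from an article is not an error. It does not cover control eligibility, which is protocol content that the article states and justifies. An analysis plan cannot create controls outside 50 to 70, nor repair a control group recruited with the wrong sex mix.

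- **Age was considered, and the sex mix may be in the figure.** Both points are fair. A reader might infer that the plan ignores age, or that the groups differ on sex by design. The documents support neither. The control range was chosen with tumour age in mind, and the control sex mix is simply not given in the text.

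- **An age or sex effect is speculative.** The Background describes HSP70 as stress-induced but says nothing about age or sex, and the expected control mean is 0. That limits how firmly an effect can be asserted. However, the mean of 0 is an expectation under test, and the same assumptions give controls an SD of 2, so variation among controls is not excluded.

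- **Adjusting for sex can mislead, because every male patient has metastatic lung cancer.** This is correct and shapes the fix. Suppose there is no sex effect, lung cancer is 1 SD higher, other tumours equal controls, and 10 controls are male. The true mean difference is 20/60 = 0.33 SD. Within women it is 10/50 = 0.2 SD; within men it is 1 SD. A pooled linear model weights these by (50 × 10)/60 = 8.33 and (10 × 10)/20 = 5, giving (8.33 × 0.2 + 5 × 1)/13.33 = 0.50 SD. Standardising to the patients' sex mix gives (50 × 0.2 + 10 × 1)/60 = 0.33 SD. The pooled coefficient therefore reweights tumour types. It does not create a signal where cancer has none, since both strata would then be 0.

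**Conclusion.** The point holds in a limited form. As written, the comparison that is to support cancer specificity has no stated control for sex and only partial control for age. Age eligibility demonstrably differs. Sex is fixed for patients and open, in the text, for controls.

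The size is conditional throughout. Under a sex effect of 0.5 to 1 SD, the false-positive rate ranges from no inflation (3 of 20 controls male) to roughly 9 to 20% (half male). Under an age effect of 0.2 SD per decade, it is about 7 to 12% for a gap of 5 to 10 years. The documents give neither effect, nor the control sex mix, nor the patients' age distribution, so no single figure is the expected error rate.

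Two stronger readings should be resisted. The power statement is not wrong; it reproduces at about 97%. Moderate confounding would also not account for the whole expected difference of 1 SD. The risk is a moderate rise in false positives, or a distorted estimate.

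**What to change.** 1. **Controls.** Unless the full protocol already sets a sex mix, recruit those not yet enrolled so that the 20 approach the patients' ratio: 20 × 50/60 ≈ 17 women and 3 men. This removes the inflation due to sex. The cost is a recruitment note.
2. **Analysis.** Keep the plain comparison and report beside it a difference adjusted for age and sex, standardised to the patients' sex mix. A women-only comparison is a simple alternative. With 50 female patients and 17 female controls, SE = 2 × √(1/50 + 1/17) = 0.56 and power is about 94%; with only 10 female controls it falls to 81%.
3. **Sensitivity.** Repeat the comparison in patients aged 50 to 70, where controls of similar age exist. The loss of precision depends on how many patients fall in that range, which is not stated.

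Age and sex are already collected, so no new data are needed. Adjustment costs a little power: it stays at about 95 to 96% under mild imbalance and drops to about 89% under strong imbalance, below the 95% that the plan states.

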Exosomes are nanovesicles (diameter 50–200 nm) secreted by numerous cell types and derived from the endosomal pathway. These extracellular nanovesicles form a bioactive cargo retrieved in several body fluids including the urine [7] and blood [8].These vesicles are composed of a cholesterol-enriched membrane enclosing proteins and genetic material. It has been shown that tumour-derived exosomes play an important role in cancer development [9]. We have shown that heat shock protein 70 is detected in the membrane of tumour-derived exosomes, in contrast to untransformed cells [10]. HSPs, also called stress proteins, are highly conserved molecular chaperones that participate in protein folding, activity, transport and stability [11, 12]. Among the different HSPs, HSP70 is induced by different types of stress and exhibits cell protective properties through its interaction with key factors in cell death pathways. HSP70 has an anti-apoptotic function, and its overexpression in cancer cells [13] confers resistance to chemotherapeutic drugs, thereby promoting cancer development [14]. Therefore, HSP70 expression level may predict chemotherapy response [15]. Indeed, HSP70 expression correlates with poor prognosis in breast, prostate, endometrial, uterine, cervical and bladder carcinomas [16]. Interestingly, HSP70 can be released in the extracellular space acting like danger signal [17]. Moreover, this protein can be expressed in a membrane-bound form, exposing in the extracellular media a 14 amino-acid C-terminal loop. We have demonstrated that HSP70 can be secreted via exosomes. In contrast to normal cells/untransformed cells, overexpression of HSP70 in cancer cells leads to its membrane translocation and its consequent detection in exosome surface. We have named these nanovesicles HSP70-exosomes [10, 18]. Their involvement in tumour growth through inhibition of the immune response and enhancement of metastatic niche formation has been demonstrated [14, 19]. These data prompted us to test whether HSP70-exosomes could be used as a cancer biomarker. Detection of HSP70-exosomes in the urine and blood of cancer patients could overcome limitations observed with CTCs since (i) exosomes are found in large amounts compared to CTCs (e.g. 53.2 ± 1.6 × 10^8^ exosomes per 10^6^ cells in the 24 h period, determined by Nanoparticle Tracking Analysis [20], (ii) HSP70 is broadly expressed in cancer cells and its overexpression in these cells leads to its membrane translocation and consequent detection in the exosomal membrane. (iii) We have patented an interference biolayer (BLI) protocol to easily capture HSP70-exosomes isolated from human fluids using as a high affinity ligand our peptide aptamer A8 (WO2015/189395, Inserm transfer, 2014).

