### Study objectives and endpoints

The primary objective of this study is to determine whether it is possible to detect and quantify HSP70-exosomes in blood in patients with solid cancers.

The secondary objectives are to:
determine whether the amount of HSP70-exosomes can be associated to:(i)response to treatment;(ii)metastatic evolution;2.determine whether the concentration of HSP70-exosomes varies with the nature of the primary tumour or the effectiveness of the treatment used;3.compare the concentrations and the early detection in HSP70-exosomes and those in circulating tumour cells determined by CellSearch, at inclusion and during patient follow-up;

The primary endpoint of the study is the blood concentration of HSP70-exosomes in malignant solid tumour patients and cancer-free controls. The secondary endpoints are as follows:
(i)the concentration of blood HSP70-exosomes in patients having a complete response, partial response, stable disease or progressive disease (RECIST criteria);(ii)the concentration of blood HSP70-exosomes in patients having metastases versus non-metastatic patients;

This study includes optional ancillary studies whose aims are to detect and quantify HSP70-exosomes in patients’ urine and to determine the genetic signature of miRNAs in HSP70-exosomes isolated from patients’ blood and urine and whether these miRNAs can be predictive of treatment response.

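### A comparison with healthy donors alone cannot confirm that exosomal HSP70 is specific to cancer, so the stated conclusion and any threshold should be limited to healthy donors

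*Protocol article*

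**What the plan says.** Under Sample size and statistical analysis, the protocol article sets feasibility of the assay as the main objective. It then adds a second, powered comparison, of the 60 patients' baseline assays with those of the 20 controls, made "to confirm that exosome HSP70 is as a cancer specific marker". The planning values are a mean of 0 in controls, about 2 in patients, a common SD of 2 and a two-sided 5% test, with power given as above 95%.

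Study objectives and endpoints gives the primary endpoint as the "blood concentration of HSP70-exosomes in malignant solid tumour patients and cancer-free controls". Study population shows who these controls are: "20 healthy volunteers with no previous cancer history, negative serology for HIV, HCV and HBC and aged 50 to 70 years old". The Abstract and the Healthy donors section describe the same single group, and no group with benign, inflammatory or other non-malignant disease is described.

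The Background says that "HSP70 is induced by different types of stress and exhibits cell protective properties" and that the protein can also be released outside the cell as a danger signal. It rests the case for specificity on a contrast between cancer cells and normal or untransformed cells. The Discussion says that a cancer-detection threshold will be set, and that a larger international study is foreseen if the pilot succeeds.

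**The concern.** Specificity is a statement about people without cancer. For a diagnostic marker, these include people who are unwell for another reason. A contrast between patients and healthy donors changes two things at once: having cancer and being ill. If non-malignant illness raises HSP70-exosomes to any degree, that rise is part of the observed difference, and the design cannot separate it out.

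The plan nevertheless commits in advance to reading a significant result as confirmation of specificity, and it intends to derive a detection threshold. The false-positive rate of that threshold would be known only for healthy donors aged 50 to 70. A follow-on study could then start from a specificity claim that this pilot did not test.

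**Working it through.** **Inputs** (Sample size and statistical analysis): 60 patients, 20 controls, means 2 and 0, common SD 2, two-sided alpha 5%.

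**1. Reproduce the stated power.**
- Standard error of the difference = 2 × √(1/60 + 1/20) = 2 × 0.2582 = 0.516.
- Noncentrality = 2 / 0.516 = 3.87, with 60 + 20 − 2 = 78 degrees of freedom.
- Power is 96.9% from the noncentral t distribution and 97.2% from the normal approximation. With 55 patients instead of 60 it is 96.6%.
- All three agree with the stated figure of more than 95%.

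**2. Ask what that power refers to.** The test statistic depends on the difference in means and not on its cause. Write the difference as *c* + *s*, where *c* is the part specific to cancer and *s* is the part due to being ill in general. The data estimate only the sum. A difference with *c* = 2 and *s* = 0 gives the same 96.9% chance of significance as one with *c* = 0 and *s* = 2.

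**3. Illustrate over a range.** The documents give no value for *s*, so the values below are assumptions. Take *c* = 0 (no cancer-specific effect) and SD 2:

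| Assumed non-specific shift *s* | Noncentrality (*s* / 0.516) | Chance that 60 v 20 is significant |
|---|---|---|
| 0 | 0 | 5% |
| 0.5 | 0.97 | 16% |
| 1.0 | 1.94 | 48% |
| 1.5 | 2.91 | 82% |
| 2.0 | 3.87 | 97% |

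The table shows only that significance can arise without specificity. It does not estimate how likely that is.

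**4. Set the sections side by side.** The claim concerns specificity for cancer. The sample without cancer is healthy donors. The Background names stress as an inducer of the protein. Its supporting laboratory contrast is with normal or untransformed cells, which does not address non-malignant disease. Nothing else described in the article measures the marker in a defined group with non-malignant disease.

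**The case against.** The strongest reply is that this is a feasibility pilot, for which healthy controls are an ordinary first step, and that the Discussion itself frames the expected contrast as one against healthy donors. That stands: the choice of controls is acceptable. The problem is the conclusion attached to them.

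A second reply is that the marker is not HSP70 in general but HSP70 on the exosome membrane, captured by an aptamer, and that patients must have performance status 0 or 1. This also has weight. No section says that non-malignant illness raises HSP70-exosomes. A reader might infer that any illness would raise them, but the documents support only that the possibility is open and untested.

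Other stronger readings also go too far:

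- *The endpoint contradicts the sample.* It does not. Healthy donors are free of cancer, and the endpoint uses a looser label for the same people.
- *No control has another illness at baseline.* The listed donor criteria do not show this. Apart from the word healthy, they cover cancer history, viral serology and age, and medical history and medication are recorded. Donors with minor conditions may be included, but only incidentally.
- *The power is overstated.* It is not. Lower figures appear only for a hypothetical comparison of patients with an ill, cancer-free group (82%, 48% and 16% if that group's mean were 0.5, 1.0 and 1.5). The study enrols no such group, and those means are assumed. Misclassification rates computed the same way are weaker still, because a normal model with mean 0 makes half of the donors' concentrations negative.

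**Conclusion.** The point holds as a limit on interpretation. A significant baseline difference would support the statement that exosomal HSP70 differs between patients with solid cancer and healthy donors. It would not confirm specificity for cancer, and a threshold derived from these data would have known specificity only against healthy donors.

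The size of any resulting overstatement cannot be given, because the documents contain no HSP70-exosome level for non-malignant illness. The conclusion rests on two things in the article: the single healthy comparator, and the Background's own account of HSP70 as stress-induced. The sample size, the test, the stated power and the feasibility rule are all unaffected. The change is worth making because it alters what the trial may conclude and costs almost nothing.

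**What to change.** 1. In Sample size and statistical analysis, replace "to confirm that exosome HSP70 is as a cancer specific marker" with: *to test whether exosomal HSP70 concentration differs between patients with solid cancer and healthy donors*.
2. In Study objectives and endpoints, call the comparator healthy donors, for consistency with the other sections.
3. Where the threshold is mentioned, state that it and its specificity apply to healthy donors only. Add that specificity against non-malignant disease is not assessed here and is left to the follow-on study.

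These are wording changes. They need no extra participants, samples or analyses. The downside is a weaker headline claim.

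Optionally, donor samples taken during a recorded intercurrent illness could be described beside the same donor's other samples, since Data collection says that "healthy donors will be followed for a year and any change in treatments or intercurrent illness". This should stay descriptive. There are only 20 donors with four visits each (20 × 4 = 80 samples, few of them likely to fall during illness). The article does not show that illness dates are recorded, and acute illness does not stand in for benign breast, ovarian or lung disease.

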In exploratory analysis, association between HSP70-exosomes concentration and treatment response (response and stable versus progressive disease) will be modelled using logistic regression and ROC curves. Area under the ROC curve will be determined with its 95% confidence interval. The same strategy will be applied to determine link between HSP70-exosomes concentration and the presence of metastases. Analyses will be repeated on subpopulation according to location of the cancer. Analyses will be performed using SAS 9.4.

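### The pooled logistic/ROC analysis of metastases mixes metastasis with tumour type, and its repeat in lung cancer cannot be estimated (20 versus 0)

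*Protocol article*

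**What the plan says.** The protocol article, under Study objectives and endpoints, lists as secondary endpoint (ii) "the concentration of blood HSP70-exosomes in patients having metastases versus non-metastatic patients". Under Sample size and statistical analysis, the exploratory part models treatment response by logistic regression and ROC curves, with an AUC and 95% confidence interval. It then says "The same strategy will be applied to determine link between HSP70-exosomes concentration and the presence of metastases", followed by "Analyses will be repeated on subpopulation according to location of the cancer". No adjustment for tumour type is mentioned, and no location is excepted from the repeat.

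The quotas that feed this analysis are:

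- Breast: "10 HER2-positive (5 non-metastatic and 5 with a first metastatic evolution"), "10 HER2-negative (5 non-metastatic and 5 with a first metastatic evolution") and "10 on hormone replacement therapy (5 non-metastatic and 5 with a first metastatic evolution").
- Ovary and lung: "10 women with an ovarian cancer grade III and IV, 10 men and 10 women with a metastatic non-small cell lung cancer".

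Table 1 admits lung patients only if their disease is metastatic. It describes the ovarian patients by stage and gives no metastatic label. One secondary objective asks whether concentration differs with the nature of the primary tumour.

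**The concern.** Because the analysis by location is a repeat, the first metastasis analysis is pooled over all 60 patients. In that pool, metastatic status and tumour type are largely tied together by design: lung can appear only on the metastatic side, and the labelled non-metastatic side is breast only. If the marker differs between tumour types, which the protocol itself treats as an open question, the pooled AUC will move away from 0.50 even when metastasis has no effect on the marker.

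What is at stake is how a named secondary endpoint is read. The Discussion foresees an international multicentre study if the pilot succeeds, and an AUC with a confidence interval that partly reflects tumour type could mislead its design. Separately, the protocol commits to a lung analysis that its own eligibility rules make impossible.

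**Working it through.** **1. The plan's own figure.** Patients: 30 breast + 10 ovary + 20 lung = 60, as stated. No sample size or power is given for the metastasis analysis.

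**2. Cross-tabulation of the quotas.**

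| Tumour | Labelled non-metastatic | Labelled metastatic | Not classified |
|---|---|---|---|
| Breast | 5 + 5 + 5 = 15 | 5 + 5 + 5 = 15 | 0 |
| Lung | 0 | 20 | 0 |
| Ovary | 0 | 0 | 10 |

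In lung the outcome is 20 versus 0, so neither a logistic model nor an AUC exists. This needs no assumption, and follow-up cannot change it because every lung patient enters with metastases.

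**3. Size of the mixing in the pooled analysis.** Assumptions, none of them from the documents: normal distributions with a common SD, no metastasis effect within any tumour type, and lung and ovary both shifted from breast by d SD in the same direction. For scale, the protocol expects patients and controls to differ by 2 with SD 2, that is 1 SD. I use d = 0.5 and 1.0.

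For one pair of patients, the probability that the shifted one is higher is Φ(d/√2): 0.638 at d = 0.5 and 0.760 at d = 1.0. The pooled AUC is the average over all metastatic/non-metastatic pairs.

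*All ovary metastatic (45 versus 15).* The metastatic side is 15 breast and 30 shifted; the other side is 15 breast.
- d = 0.5: (15 × 0.5 + 30 × 0.638)/45 = 26.64/45 = 0.59
- d = 1.0: (15 × 0.5 + 30 × 0.760)/45 = 30.3/45 = 0.67

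*Five ovarian patients non-metastatic (40 versus 20, 800 pairs).*
- d = 0.5: (225 × 0.5 + 75 × 0.362 + 375 × 0.638 + 125 × 0.5)/800 = 0.55
- d = 1.0: (225 × 0.5 + 75 × 0.240 + 375 × 0.760 + 125 × 0.5)/800 = 0.60

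*All ten non-metastatic (35 versus 25, 875 pairs).*
- d = 0.5: (225 × 0.5 + 150 × 0.362 + 300 × 0.638 + 200 × 0.5)/875 = 0.52
- d = 1.0: (225 × 0.5 + 150 × 0.240 + 300 × 0.760 + 200 × 0.5)/875 = 0.54 to 0.55

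Share of trials rejecting at a nominal two-sided 5% (t-test, 20,000 simulated trials):

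| Ovarian patients counted non-metastatic | d = 0.5 | d = 1.0 |
|---|---|---|
| 0 of 10 | 18% | 53% |
| 5 of 10 | 10% | 21% |
| 10 of 10 | 5% | 6% |

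**4. Opposite shifts.** If all ovary counts as metastatic but lung is d higher and ovary d lower than breast, the two partly cancel.
- d = 0.5: (15 × 0.5 + 20 × 0.638 + 10 × 0.362)/45 = 0.53
- d = 1.0: (15 × 0.5 + 20 × 0.760 + 10 × 0.240)/45 = 0.56

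Rejection is then 5% to 7%. The cancellation depends on ovary sitting on the metastatic side. With all ten on the other side, opposite shifts of 0.5 SD give (225 × 0.5 + 450 × 0.638 + 200 × 0.760)/875 = 0.63.

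**5. Breast only (15 versus 15).** There is no tumour-type difference. Hanley–McNeil standard error at AUC 0.70: A/(2 − A) = 0.5385 and 2A²/(1 + A) = 0.5765. The variance is [0.21 + 14 × (0.5385 − 0.49) + 14 × (0.5765 − 0.49)]/225 = 0.00933, so SE = 0.0966 and the 95% half-width is 1.96 × 0.0966 = 0.19. The same formula at 45 versus 15 gives 0.14. Power for a 1 SD difference (normal approximation) is Φ(1/√(2/15) − 1.96) = Φ(0.78) = 78%.

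**The case against.** The other side has four good arguments.

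- The analysis is called exploratory, and no decision rule or sample size rests on it. This stands and limits the weight of the point.
- The repeat by location already produces the 15 versus 15 breast comparison. This also stands: the sound analysis is in the plan, but it is not put ahead of the pooled one.
- Covariates may be set out in an analysis plan that is not shown. This stands only in part. Adjusting for tumour type would leave breast as the source of information on metastasis (with ovary, if that group turns out mixed). No analysis plan can supply non-metastatic lung patients.
- The larger figures assume that all ovarian patients count as metastatic and that lung and ovary shift equally in the same direction. This stands, and the results above vary accordingly.

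A reader might go further in three ways that the documents do not support. One is that every non-metastatic patient has breast cancer: that is true of the labels, but stage III ovarian patients are unclassified. Another is that the pooled AUC measures tumour type alone: with ovary counted as metastatic, one third of that side (15 of 45) is still breast. The third is that the treatment-response model is flawed because resected patients cannot be graded by RECIST. The response endpoint is worded for patients who have a RECIST category, and nothing in the article places patients without one in the model.

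**Conclusion.** The concern holds in a limited form. Two things follow from the quotas alone: the lung repeat cannot be estimated (20 versus 0), and the pooled comparison is unbalanced by tumour type, with all lung patients on the metastatic side however ovary is classified.

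The size of the resulting bias depends on assumptions. With no metastasis effect and equal shifts of 0.5 or 1.0 SD, the pooled AUC is about 0.59 or 0.67 if ovary counts as metastatic, and about 0.55 or 0.60 if half of it does not. It is small if all ovary counts as non-metastatic and shifts with lung. That spread shows that the undefined status of stage III ovarian disease matters to the result.

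The feasibility rule (47 of 55) and the comparison of patients with controls are unaffected. The point deserves correction, but it is not a must-fix.

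**What to change.** In the exploratory analysis text and for secondary endpoint (ii):

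- Make the breast-only comparison, 15 versus 15, the lead metastasis analysis.
- Drop the pooled unadjusted AUC, or report it with a statement that it is confounded by tumour type.
- State that the repeat by location cannot be done in lung.
- Define, for this analysis, whether stage III ovarian cancer counts as metastatic, and run the ovarian repeat only if both classes are present.

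These are changes of wording; recruitment and sampling stay as they are. The cost is precision: at an AUC of 0.70 the 95% half-width is about 0.19 with 15 versus 15, against about 0.14 with 45 versus 15.
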